## Epidemiology

Malaria is a leading cause of morbidity and mortality and an important contributor of poverty in Africa where it accounts for more than 1 million deaths and an economic cost equivalent to USD 12 billion each year. It has been described as Africa’s public health enemy number one and it is estimated that 90% of global malaria cases and 80% of malaria deaths occur in sub-Saharan Africa. Children under five years of age and women in their first or second pregnancy are the main sufferers. Other vulnerable groups include refugees and short-term visitors from non-endemic areas. The visitors include tourists and investors who are essential for Africa’s economic revival.

In terms of labour charge and drop of economic activity, the cost of malaria is enormous. Worldwide, malaria victims are reported to occupy 3 out of 10 hospital beds; in Africa, where transmission which reaches a peak at harvest time, and affects children under 5 years of age, a “simple” malarial attack amounts to 10 days of work14. Thus, malaria is both the poor man’s disease and a cause for poverty. The economic growth of “high transmission countries” has always been inferior to the growth of non-malarial countries.

In Burkina Faso, malaria is endemic. Transmission remains constant, with a peak during the rainy season (June to October), *P.falciparum* is responsible for more than 90% of all clinical malaria cases. The major vectors are *Anopheles gambiae s.s*., *An. arabiensis et An. Funestus*. Children under 5 and pregnant women are the populations at highest risk.

During the five months when transmission reaches a peak, these age-brackets suffer multiple malaria episodes, with an annual malaria death rate reaching 15,00015. In the country’s hospitals, malaria is reportedly responsible for 30.7% of all hospitalisations with a mortality rate of 23%15.

Balonghin, the selected study area, is a village about 50km out of Ouagadougou. The CNRFP have established a Vaccinology centre within this village. The study participants will come from this village and surrounding ones covered within the CNRFP characterised site with a total population of 100,781 inhabitants.

Of these 18.75 percent are children within the targeted age group for this study. The inhabitants mainly belong to the Mossi (90%) and Fulani (5%) ethnic groups. The adult illiteracy rate is high reaching more than 71%. Populations regard malaria as a major Public Health problem, but the knowledge about this disease and above all, its prevention and the way it should be cured remains inadequate. Traditional medicine still plays an important part in the cure of all diseases as more than 65% of the families use it in the first place.

Unfortunately, control measures currently in use are failing owing to poor healthcare delivery systems, emergence of parasite resistance to cheaper and effective drugs as well as limited effectiveness of vector control due to insecticide resistance and environmental concerns.

Failure in the current control measures call for an accelerated development of malaria vaccines as a potential additional tool in the arsenal against malaria. Reasons for lack of effective interventions for malaria have been eloquently addressed in various publications, but prominent among these is the lack of financial returns to investments on research in the development of new anti-malarial drugs and vaccines.

## Name and description of investigational product

MSP3, a candidate malaria vaccine, is a long synthetic peptide that uses a 181-276 amino acid sequence. It is available in a multi-dose vial presented lyophilised, and looks like amorphous white powder. The vaccine is produced by SYNPROSIS in France.

## Summary of findings from non-clinical studies

***In vivo* passive transfer** experiments in *P. falciparum* infected SCID mice: [name] *et al*. have recently described *P. falciparum* growth in immuno-deficient mice grafted with human erythrocytes. They report the potential of this new mouse model for vaccine development against *P.falciparum* malaria determined by studying the effect of antibodies in passive transfer experiments, the effect of which is well established in humans16. Results show that African adult immunoglobulin strongly reduces *P. falciparum* parasitaemia in a similar fashion to that reported in humans, provided the mice are reconstituted with human monocytes (HuMN). In contrast neither immunoglobulin nor HuMN alone had any direct effect upon the circulating parasitaemia in mice when added separately.

These experiments were extended to assess the *in vivo* effect of epitope-specific antibodies. Human antibodies were affinity-purified on peptides derived either from the Ring Erythrocyte Surface Antigen (RESA) or the Merozoite Surface Antigen-3 (MSP3), and their specificity and titers determined. Results show that the inoculation of low concentrations of anti-MSP3b, but not anti-RESA antibodies, together with HuMN suppress *P. falciparum* parasitaemia in mice in a consistent manner. The rate at which parasitaemia decreased was as fast or faster than that induced by total African IgG, and as fast as that induced by chloroquine17. That such a profound biological effect can be obtained using only a minor subset of the total anti-malarial antibodies, i.e. those affinity purified on a single peptide from one of the numerous *P. falciparum* proteins, is striking. However, this result is in keeping with immuno-epidemiological observations, which show a 90% positive predictive value for the level of clinical protection associated with IgG3 antibodies directed to the same MSP3b peptide. The strong effect in mice of small amounts of anti-MSP3 Abs is in agreement with the relatively low levels of the same Abs in populations with clinical protection living in holo-endemic areas. There is therefore a convergence of data obtained by three different means, i.e. under *in vitro* conditions (ADCI), *in vivo* conditions in mice (in Scid), or in humans (by immuno-epidemiological methods). Results demonstrate the value of the model, in which antibodies with distinct specificities can be evaluated sequentially in the same animal, and they also reinforce the potential of MSP3 for vaccine development.

**A recombinant human antibody** was obtained by preparing RNAm from lymphocytes from immune African subjects; cloning cDNA in a filamentous phage capable of producing the Fab’2 immunoglobulin fragments on its surface. Abs specific to MSP3 were isolated by the DG210 antigen through the panning of phages on coated patches. Then, build-ups integrating the heavy-chain genes, namely IgG1 or IgG3, were prepared. Antibodies were produced from CHO cells and then purified. With a concentration of 3mg/l, Ab RAM1 IgG1 produces in vitro an ADCI effect in presence of human monocytes whose activity is equal or superior to that obtained with the African IgG pool. Injected in *P.falciparum* infected SCID mice, it produces complete clearance of parasitaemia within four days whereas an Ac combining an anti-rhesus control has no effect.

**Louis Miller’s team at NIH immunised three series of 7 Aotus**, using either Ag control, or MSP1, or MSP3 with Freund’s adjuvant. Results show partial protection, with maximum parasitaemia of 5%, in 5 out of 7 Aotus receiving MSP1 Stronger protection (maximum parasitaemia 0.9%) was observed in 6 out 7 MSP3 vaccinated monkeys. In MSP3 immunised animals there was a correlation between Ab anti-MSP titres, after immunisation and before challenge, and the observed protection. In MSP1 immunised animals, a) there was no correlation between Ab anti-MSP1 titres and protection, b) a correlation was observed in MSP1 vaccinated animals between challenge driven Ab anti-MSP3s and protection. These results agree with the protection induced in *saimiri* monkeys by MSP3 adjuvanted with Montanide or ASO218.

**The sequence analysis of the MSP3 C-terminal area** was piloted by Australian teams on more than 20 isolates and in Denmark, by M. Theisen on more than 70 isolates. The results show an absolute conservation of the protein sequence and more surprisingly of the nucleotide sequence (no “synonym” codon, that is to say a distinct codon coding for the same amino acid.)

**Studies on MSP3 Immunogenicity** were performed using the MSP3b peptide, three multiple branches peptides (octopus), recombinant DG 210, recombinants covering the C-Terminal expressed in the PGEX vector, the pTCr his vector, the yeast, the Long Synthetic Peptide with a series of adjuvant representative of several existing class: Complete and incomplete Freund adjuvants, alum, ISA 51 and ISA 720 montanide, titermax, Ribi adjuvant, one of Aventis’s experimental adjuvants, one from OM-pharma, GSK’s SBAS2, and the priming combination by MSP3-PPD BCG-boosting. In mice, except for alum, all the formulations proved immunogenic to different degrees, some of them were tested on Saimiri and proved to be efficient5. Nevertheless, there still wasn’t a parallel in ELISA and in titres on native proteins.

This body of convergent results makes MSP3 a promising vaccine candidate.

## Clinical experience with MSP 3 LSP

**A first phase 1a trial** was conducted in Switzerland, on healthy adults, who had never been exposed to malaria. The MSP3-LSP vaccine was administered to 35 volunteers, in 3 subcutaneous injections at 0, 1 and 4 months. Four different dosages: 10µg, 20µg, 30µg or 100µg and two adjuvants, Montanide 720 and Aluminium hydroxide were evaluated. The following table shows the distribution of subjects by dose and by adjuvant:

| **Groups** | **Dosage** | **Adjuvant** | **Number of subjects** |
| --- | --- | --- | --- |
| M10-10-10 | 10 µg LSP | Montanide 720 | 6 |
| M30-30-10 | 30 µg LSP | Montanide 720 | 6 |
| M100-10-10 | 100 µg LSP | Montanide 720 | 5 |
| M20-20-20 | 20 µg LSP | Montanide 720 | 6 |
| A30-30-30 | 30 µg LSP | Alum | 6 |
| A100-10-10 | 100 µg LSP | Alum | 6 |

Immediate local and systemic tolerance was monitored for the hour following the injection and again two days after vaccination. Humoral and cellular immune responses and the functionality of the immune response were assessed one month after each injection and five and nine months after the booster dose.

The vaccine showed a very good systemic tolerance, whatever the adjuvant or dose, with no systemic reactions observed during the study. In contrast, local tolerance was clearly linked to dose, adjuvant and injection number. Because of large local reactions, with 10cm indurations, the second scheduled 100µg injections were replaced by 10µg injections for both adjuvants. After the second 30µg MSP3, Montanide adjuvated dose, the increasing local reactions observed led the investigator to replace the third dose with a 10µg dose. With a 30µg MSP3 vaccine adjuvanted with Aluminium hydroxide, the growing number of local reactions only emerged after the third dose had been delivered. (See following figures).

[figure not shown]

The immune response induced by MSP3’s different formulations in humans, was higher than the response observed in pre-clinical studies. Interestingly, the adjuvant effect of aluminium hydroxide in humans was greater in humans than in monkeys or mice, and it was comparable to the adjuvant effect of Montanide 720. The immune response was maintained nine months after the booster dose was injected. The functionality of the immune response, as measured by the ADCI assay, showed that antibodies induced by vaccination could lead to an inhibition of *P. falciparum.*

To conclude, at a dose of 30µg, the MSP3 vaccine was well-tolerated by healthy adults not exposed to malaria, and led to the production of antibodies capable, in vitro, of neutralizing the *P. falciparum* parasite19.

**The second study was a phase Ib trial** conducted in Burkina Faso among semi-immune adults. A total of 30 participants enrolled ad all of them received three vaccine doses in the same schedule of 0, 1 and 4 months. All participants completed the study *per protocol*.

No immediate local reactions of any kind were recorded after any of the three vaccinations. During the 14 days follow-up period after each vaccination no local reactions that prevented normal daily activity were recorded. The most frequently reported local symptom in both vaccine groups was mild swelling (size less than 3 cm) at the injection site lasting up to 6 days after the vaccination. Only one participant in the tetanus group reported a mild induration lasting 16 days which resolved without sequellae. Local adverse reactions/events were recorded with similar frequency in the two vaccine groups.

Only one participant in the MSP3-LSP group experienced an immediate systemic reaction, an episode of mild tachycardia, possibly related to the vaccination, which lasted for 2 hours. No action was taken and this was not considered to be a serious adverse event.

Two individuals in the MSP3-LSP vaccine group had a malaria episode compared with one individual in the tetanus group. The most frequent syndrome was bronchitis (7 cases in the MSP3-LSP group and 4 cases in the tetanus group). No individuals experienced diffuse erythema, urticaria, Quincke’s oedema, asthma, malaise, drowsiness, experienced pallor, sweating, tachycardia (except the immediate reaction described above), loss of appetite, flu-like syndrome. All symptoms resolved without sequellae.

Eosinophilia was observed in all participants at some point during follow-up except one, with similar frequency in the two vaccine groups. Two individuals in the MSP3-LSP group and one in the tetanus group experienced hyperglycaemia. In all three individuals the hyperglycaemia was transient and in none was it considered clinically significant. None of the haematological abnormalities were judged to be related to the study vaccines.

|  | **MSP-3 LSP*** | | | **Tetanus*** | | |
| --- | --- | --- | --- | --- | --- | --- |
|  | Dose 1  N=15 | Dose 2  N=15 | Dose 3  N=15 | Dose 1  N=15 | Dose 2  N=15 | Dose 3  N=15 |
| Pain | 6 | 5 | 5 | 7 | 8 | 3 |
| Erythema | 0 | 1 | 1 | 1 | 1 | 0 |
| Induration | 0 | 2 | 3 | 3 | 4 | 3 |
| Swelling | 4 | 8 | 7 | 8 | 6 | 6 |
| Pruritus | 2 | 0 | 1 | 1 | 0 | 3 |
| Local heat | 0 | 0 | 0 | 0 | 0 | 0 |

In summary, both vaccines were well tolerated; no unexpected adverse reactions were reported. No serious adverse events were observed. The reactogenicity profile of the MSP3-LSP vaccine did differ substantially from that of tetanus vaccine in male adults.

No detectable Humoral immune response was induced by the MSP3-LSP vaccine. Lympho-proliferation in response to stimulation with PHA antigen was similar in the two vaccine groups. The response in the tetanus vaccine group to stimulation with tetanus toxoid antigen increased following vaccination, while the response in the MSP3-LSP group was unchanged after vaccination. The response in the MSP3-LSP vaccine group to stimulation with MSP3-LSP antigen increased after vaccination, while that in the tetanus group appeared unchanged

The pattern of IFN gamma responses to stimulation with PHA antigen was very similar in the two groups with a slight decrease between Day 0 and Day 56. IFN gamma responses to stimulation with tetanus toxoid antigen were unchanged post vaccination. IFN gamma responses to stimulation with MSP3-LSP antigen appeared to remain stable in the MSP3-LSP group after vaccination, while in the tetanus group, they showed a similar decline to that observed with PHA.

## Rationale

The phase 1 trial results in young Swiss adults highlight the MSP molecule’s vaccine potential. As the next step in the clinical development of this vaccine, the phase Ib trial in Burkina Faso has further demonstrated that the MSP 3 LSP vaccine is safe even in populations exposed to *P. falciparum.* A desirable property of the vaccine shown through the second study was that the local reactogenicity in *P.falciparum* exposed individuals after the first injection was less than that observed after the second and third doses in Swiss volunteers.

Having met the preset go criteria for the adult studies, the vaccine now requires approaching the ultimate target population in a stepwise manner. A vaccine intended for developing countries, can only be realistically deployed through the Expanded Programme on Immunisation (EPI). In order to fit in that programme, the schedule of administering our vaccine has to be changed so that it could fit in. All the clinical experience with this vaccine so far has been with adults. We have decided to be cautious and not presume its safety in children; therefore, both the 30µg and 15µg of the MSP 3 LSP vaccine will be evaluated. Hepatitis B vaccine has been selected as control vaccine for the following technical and ethical reasons:

- It has recently been adopted and incorporated within the Burkina Faso EPI immunisation programme, and therefore is clearly of public health benefit;
- Can be administered in a schedule acceptable for evaluating our study vaccine;
- The targeted children in this trial would not have received it; therefore it will specifically be on benefit to them.

# Trial Objectives

## Primary Objective

**To assess the safety and reactogenicity** of 3 doses of 15 µg and 30 µg MSP3 LSP adjuvanted in Aluminium hydroxide given at D0, D28 and D56 in healthy children 1-2 years old in Burkina Faso on the following:

1. Immediate reactogenicity (within 1 hour, with emphasis on allergic reactions),
2. Local and systemic reactogenicity during the 7 days following the vaccine administration(day of vaccination and 6 subsequent following days)
3. Unsolicited adverse events occurring within 28 days following each vaccination
4. Serious adverse events (SAE) throughout the study period.

## Secondary Objectives

1. To assess the humoral immune response to the vaccine antigen by measuring the increase in the level of antibodies through measuring:

IgG, Ig M and IgA to MSP3-LSP and to MSP3 peptides (a,b,c and d )

Isotypes IgG1, IgG2, IgG3, IgG4, (MSP3-LSP peptide)

Using ELISA, before and four weeks after each vaccination, as well as 4 and 9 months after the last injection

1. **To assess the cellular immune response** to the vaccine antigens by measuring: the number of cells producing IFNγ/106 cells by Elispot to MSP3-LSP and MSP3 peptides a, b, c and d

Before and four weeks after the second and the third injection

## Tertiary or exploratory objectives

1. To evaluate IgG ability to recognise the native protein on Merozoite by using Western Blot method.
2. To evaluate functionality of IgG by using the ADCI technique.

# Study Design Overview

| **Study Days** | | D0 | | D14 | | D28 | | | D42 | | D56 | | D70 | | D84 | D98 |  |  |  |
| --- | --- | --- | --- | --- | --- | --- | --- | --- | --- | --- | --- | --- | --- | --- | --- | --- | --- | --- | --- |
|  | |  | |  | |  | | |  | |  | |  | |  |  |  |  |  |
|  |  |  |  | | |  |  | | | |  | | | |  |  |  | |  |
|  |  |  |  | | |  |  | | | |  |  | | | Group 1 (15µg) | |  | |  |
|  |  |  | | | |  | | | | |  | | | |  | |  | |  |
|  |  | Vacc 1 | | | | Vacc 2 | | | | | Vacc 3 | | | |  | |  | |  |
|  |  |  | |  | |  | | |  | |  | |  | |  |  |  | |  |
|  |  |  | |  |  | | | |  |  | | |  | | | Group 2 (30µg) | | |  |
|  |  |  | |  | |  | | |  | |  | |  |  | |  |  | |  |
|  |  |  | | Vacc1 | |  | | | Vacc2 | |  | | Vacc3 |  | |  |  | |  |
|  |  |  | | | |  | |  |  | |  | | |  | | |  |  |  |
|  | |  | | | |  | | | | |  | | |  | | |  | |  |
|  | |  | Safety reports post 7 days follow up | | | | | | | | Vacc = Vaccination | | |  | | |  | |  |

|  |  | | |  | |  |  |  |  | |  | |  | |  |  |  |  | |  |
| --- | --- | --- | --- | --- | --- | --- | --- | --- | --- | --- | --- | --- | --- | --- | --- | --- | --- | --- | --- | --- |
|  |  | | |  | |  |  |  |  | |  | |  | |  |  |  |  | |  |
|  |  | | |  | |  |  |  |  |  |  |  |  |  |  |  |  |  | |  |
|  |  | | |  | |  |  | **Vacc 1** |  | | **Vacc 2** | | **Vacc 3** | |  | BS |  | BS | BS |  |
|  |  | | |  | | **Randomization** | | *MSP3 BS* |  | | *MSP3 BS* | | *MSP3 BS* | |  |  |  |  | |  |
|  |  | | |  | |  |  | |  | |  | |  |  |  |  | |  |
|  |  | | |  | |  |  | |  | |  | |  |  |  |  | |  |
| BS |  | | |  | |  |  | |  | |  | |  |  |  |  | |  |
|  |  | | |  | |  |  | |  | |  | |  |  |  |  | |  |
|  |  | | |  | |  |  |  |  | |  | |  | |  |  |  |  | |  |
|  |  | | |  | |  |  |  |  |  |  |  |  |  |  |  |  |  | |  |
|  |  | | |  | |  |  | **Vacc 1** |  | | **Vacc 2** | | **Vacc 3** | |  | BS |  | BS | BS |  |
|  |  | |  | |  | |  | *Hepatitis B BS* |  | | *Hepatitis B BS* | | *Hepatitis B BS* | |  |  |  |  | |  |
|  |  | | | | |  |  |  |  | |  | |  | |  |  |  |  | |  |
|  |  | | |  | |  |  |  |  |  |  |  |  |  |  |  |  |  | |  |
| **Clinic  Visit 1**  Day -28 to -14 | |  | | | |  |  | **Clinic  Visit 2**  Day 0 |  | | **Clinic  Visit 3**  Day 28 | | **Clinic  Visit 4**  Day 56 | | **Clinic  Visit 5** Day 84 | | **Clinic  Visit 6** Day 168 | **Clinic  Visit 7** Day 365 | |  |
|  |  | | | | |  |  |  |  | |  | |  | |  | |  |  | |  |
|  | **SCREENING** | | | | | | | **VACCINATION** | | | | | | | | | **LONG TERM SAFETY FOLLOW UP** | | |  |
|  |  | | | | | | | **DOUBLE-BLIND PHASE** | | | | | | | | | **SINGLE-BLIND PHASE** | | |  |
|  |  | | | | |  |  |  |  | |  | |  | |  | |  |  | |  |
| **BS;** Blood Sample. **Vacc;** Vaccination. | | | | | | | | | | | | | | | | | | | | |
|  | | | | | | | | | | | | | | | | | | | | |

- Double blind (observer blind, participant blind), randomized, controlled, dose escalation, Age de-escalation, phase Ib study
- One study centre,
- Two parallel groups
- Group 1: 23 subjects (15 subjects receiving MSP-3 vaccine 15 µg and 8 subjects receiving Hepatitis B vaccine).
- Group 2: 22 subjects (15 subjects receiving MSP-3 vaccine 30 µg and 7 subjects receiving Hepatitis B vaccine)
- Immunization schedule will be 0, 1, and 2 months for all cohorts and provisionally as following for each group:
  - Study days 0, 28 and 56 for group 1
  - Study days 14, 42, 70 for group 2
- Vaccinations of groups 1 and 2 will be staggered: immunization in group 2 will start 2 weeks after group 1. This interval may be extended if deemed necessary due to SAEs or other safety concerns.
- Randomization will be done for each group at the times of first vaccinations.
- Route of inoculation will be by subcutaneous injection into right or left deltoid (alternately).
- Each child will be observed for at least 60 minutes after vaccination to evaluate and treat any acute adverse events (AEs)
- Study duration will be approximately 13 months per subject.
- Seven (7) day follow-up period for solicited adverse events (day of vaccination plus 6 subsequent days)
- Twenty eight (28) day follow-up period for unsolicited adverse events (Vaccination day plus 27 subsequent days)
- Follow-up of serious adverse events (SAE’s) for 12 months after the first dose of study vaccine (9 months after dose 3)
- At the end of the follow-up period for unsolicited AEs (i.e., one month after the third dose), subjects will be followed by field workers at home at monthly intervals to record SAEs.
- Data collection: conventional Case Report Form (CRF).

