| **Primary**  **Evaluation Criteria** | The primary endpoints are measures of the safety and reactogenicity of the vaccine as determined by:   1. Occurrence of solicited symptoms during a 7 day follow-up period after each vaccination (day of vaccination and 6 consecutives days) 2. • Occurrence of unsolicited symptoms during a 28 day follow-up period after each vaccination 3. • Occurrence of serious adverse events throughout the study period |
| **Secondary Evaluation Criteria** | 1. **Humoral response to vaccine antigens:**   Post vaccination levels of IgG, IgA and IgM, expressed in arbitrary units (ng/ml), relative to the pre-vaccination level (D0): D28/D0, D56/D0, D84/D0, D168/D0, and D365/D0.   1. **Cellular immune response to vaccine antigens:**   The number of cells producing IFNγ by Elispot expressed in number of spots /106 cells |
| **Exploratory Evaluation Criteria** | **To evaluate IgG ability to recognise the native protein on Merozoite by using WB**   - **Parasite inhibition by ADCI (SGI %) on D0, D84, D168 and D365. (only if isotype study shows the production of MSP3 specific cytophilic Abs in > 30% of volunteers)** |
| **Statistical Methods** | The analysis shall be descriptive  The final analysis is planned 1 month post Dose 3 to evaluate whether the safety GO/No GO criteria are met to proceed to a phase 2b in. An annex safety analysis will be performed at the end of the study, 9 months post Dose 3. |

| Study phases | Screening | Vaccination Phase (Double blind) | | | | | | | | | | Follow up (Single blind) | | |
| --- | --- | --- | --- | --- | --- | --- | --- | --- | --- | --- | --- | --- | --- | --- |
| Clinic Visit | **V1** | **V2** |  | **V3** | **V4** |  | **V5** | **V6** |  | **V7** | **V8** | **V9** |  | **V10** |
| **Home visits1** |  |  | **HV1-5** |  |  | **HV6-10** |  |  | **HV11-15** |  |  |  | **HV16-21** |  |
| **Trial Timelines (Days,)** | **D-28** | **D0** | **D1-D5** | **D6** | **D28** | D29-D35 | **D36** | **D56** | **D57-D62** | **D63** | **D84** | **D168** | **D196-D337** | **D365** |
| **Time Windows (Days)** |  |  4 D |  |  |  4 D |  |  |  4 D |  |  |  4 D |  7 D |  7 D |  14 D |
| **Study procedures** |  |  |  |  |  |  |  |  |  |  |  |  |  |  |
| Screening consent |  |  |  |  |  |  |  |  |  |  |  |  |  |  |
| Study Consent |  |  |  |  |  |  |  |  |  |  |  |  |  |  |
| Check of inclusion /non Inclusion Criteria |  |  |  |  |  |  |  |  |  |  |  |  |  |  |

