| Medical History |  |  |  |  |  |  |  |  |  |  |  |  |  |  |
| Worm infestation treatent |  |  |  |  |  |  |  |  |  |  |  |  |  |  |
| Physical Examination |  |  |  |  |  |  |  |  |  |  |  |  |  |  |
| Check of contra-Indications to vaccination |  |  |  |  |  |  |  |  |  |  |  |  |  |  |
| Randomisation |  |  |  |  |  |  |  |  |  |  |  |  |  |  |
| Vaccine administration |  | **** |  |  | **** |  |  | **** |  |  |  |  |  |  |
| Check of elimination criteria |  |  |  |  |  |  |  |  |  |  |  |  |  |  |
| Recording of medication |  |  |  |  |  |  |  |  |  |  |  |  |  |  |
| **Safety and reactogenicity data collection** |  |  |  |  |  |  |  |  |  |  |  |  |  |  |
| Immediate post-vaccine surveillance (60’) |  | x |  |  | x |  |  | x |  |  |  |  |  |  |
| Recording of solicited Local & Systemic Events/Reactions |  |  | x | x | x | x | x | x | x | x |  |  |  |  |
| Recording of unsolicited adverse events |  |  |  |  |  |  |  |  |  |  |  |  |  |  |
| Recording of Serious Adverse Events |  |  |  |  |  |  |  |  |  |  |  |  |  |  |
| **Laboratory analysis** |  |  |  |  |  |  |  |  |  |  |  |  |  |  |
| Complete blood count |  |  |  |  |  |  |  |  |  |  |  |  |  |  |
| Creatinine, ALT/AST, Biluribin |  |  |  |  |  |  |  |  |  |  |  |  |  |  |
| Humoral response measurement |  |  |  |  |  |  |  |  |  |  |  |  |  |  |
| Cell mediated immunity measurement |  |  |  |  |  |  |  |  |  |  |  |  |  |  |
| Functional assays (ADCI) |  |  |  |  |  |  |  |  |  |  |  |  |  |  |
| Anti-HBs antibodies |  |  |  |  |  |  |  |  |  |  |  |  |  |  |
| Western blot |  |  |  |  |  |  |  |  |  |  |  |  |  |  |
| **Analysis and reporting** |  |  |  |  |  |  |  |  |  |  |  |  |  |  |
| Final Analysis |  |  |  |  |  |  |  |  |  |  |  |  |  |  |
| Annex safety Analysis |  |  |  |  |  |  |  |  |  |  |  |  |  |  |

**1**  from the first home (HV1) to HV15 the visit will be daily. The visits wil be monthly from HV16 to HV21

| **List of Abbreviations** |
| --- |

95% CI 95% Confidence Interval

AIDS Acquired Immunodeficiency Syndrome

AMANET African Malaria Network Trust

ADCI  Antibody Dependent Cellular Inhibition of parasite growth assay

CRF  Case Report Form

CNRFP Centre National de Recherche et de Formation pour le Paludisme

CTA Centre des Traitements Ambulatoires

DSMB Data and Safety Monitoring Board

EC  Ethics Commitee

ELISA Enzyme Linked Immuno Sorbent Assay

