### Trial Calendar

Screening for potential study participants is planned to start in February 2007. The first participant is planned to be recruited in March 2007. The recruitment period will last for four weeks. Vaccinations would then start in March, and will be staggered starting with Lower dose of MSP3 (15 µg) and then the Higher dose (15 µg) 14 days later. Each participant will be followed-up for a total period of one year from the first injection. The study has 11 scheduled clinic visits and 21 scheduled home visits, but participants will be under strict instructions to report at the unit should they feel unwell at any time. The planned final analysis at 1 month post vaccination 3 will look only at safety data to evaluate the go/no go safety criteria for pursuing the clinical development plan.

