### Vaccination and serological schedule

Scheduled clinic visits are planned at day -28, 0, 6, 28, 36, 56, 63, 84, 168 and 365. Three vaccine doses will be administered by subcutaneous injection (day 0, 28 and 56). As shown in the flow chart (see page 9), participants will be monitored for the hour following vaccination, then a field worker will visit them at home on each of the 5 days following the injection. The patient will come back to the clinic at the 6th day following each immunization to be assess by a study clinician. Six serological blood sampling points have been planned on days 0, 28, 56, 84, 168 and 365.

Biological evaluations will also be done on days -28, 0, 6, 28, 36, 56, 63, 84 and 365. Apart from these standard examinations, other tests may be performed if deemed necessary.

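### Monthly home visits to record SAEs are promised from D84, but the visit schedule starts them at D196 and leaves 84 days with no scheduled contact

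*Protocol*

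**What the plan says.** Section 3 ties the start of home follow-up to a fixed point: "At the end of the follow-up period for unsolicited AEs (i.e., one month after the third dose"). From then on, "subjects will be followed by field workers at home at monthly intervals to record SAEs". The same section sets SAE follow-up at 12 months after the first dose.

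The schedule is set out in four other places:

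- **Synopsis flow chart.** V8 is at D84 and V9 at D168. Home visits HV16-21 come after V9, in the column order "D168 | D196-D337 | D365".
- **Flow-chart footnote.** "The visits wil be monthly from HV16 to HV21".
- **Section 5.2.3, Trial Calendar.** "The study has 11 scheduled clinic visits and 21 scheduled home visits". The same sentence adds that participants are told to report to the unit if they feel unwell at any time.
- **Section 5.2.4, Vaccination and serological schedule.** "Scheduled clinic visits are planned at day -28, 0, 6, 28, 36, 56, 63, 84, 168 and 365".

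On timing, section 5.2.3 states: "Vaccinations would then start in March, and will be staggered starting with Lower dose", with the higher dose following 14 days later. Section 1.2 describes malaria transmission "with a peak during the rainy season (June to October").

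**The concern.** Section 3 and the schedule cannot both be followed. Field teams usually work from the flow chart and the visit numbers. A team that did so here would make no planned visit between D84 and D168, although section 3 commits it to monthly ones.

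SAEs throughout the study are one of the primary endpoints, and section 13.4.2.1 has active SAE monitoring run until the last visit of the last subject. In the uncovered interval, SAE capture would rest on families coming forward and on recall at D168. Section 1.2 gives reasons not to lean on that: more than 65% of families turn first to traditional medicine, and malaria is said to account for 30.7% of hospitalisations. Hospitalisation is an SAE criterion in section 13.1.2, and on the planned start date the interval lies largely within the high-transmission months. At stake are the completeness, timeliness and dating of late SAEs.

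**Working it through.** **Inputs**

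- Dose 3 at D56; clinic visits at D84 and D168 (synopsis, section 5.2.4).
- HV1-5, HV6-10 and HV11-15 after the three doses; HV16-21 over D196-D337 (synopsis).
- 21 home visits (section 5.2.3).
- Visit windows of 4 days at D84 and 7 days at D168 (synopsis). The sign is not legible in the text, so plus or minus is assumed.
- Vaccination starting in March 2007, second group 14 days later (section 5.2.3). The exact day is not given. First doses from 1 March to 14 April 2007 (31 March plus 14 days) are assumed.
- Peak season 1 June to 31 October: 30 + 31 + 31 + 30 + 31 = 153 days (section 1.2).

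**1. Reproduce the plan's 21 home visits.** 5 + 5 + 5 + 6 = 21, which agrees with section 5.2.3. Six visits over D196-D337 are (337 - 196)/5 = 28.2 days apart. The first is 196 - 168 = 28 days after V9 and the last is 365 - 337 = 28 days before V10. The monthly series in the chart is therefore complete and begins after D168. No unlisted visit is left over for D112 or D140.

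**2. Count what section 3 implies.** Steps of 28 days from D84 give D112, D140, D168, D196, D224, D252, D280, D308 and D336. D168 is already clinic visit V9, so 8 home visits are needed against 6 scheduled. The total would be 15 + 8 = 23. The two missing are at about D112 and D140.

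**3. Length of the gap.** 168 - 84 = 84 days, or 84/365 = 23% of the year. With the D84 visit 4 days late and the D168 visit 7 days early, it is 161 - 88 = 73 days.

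**4. Position in the season.** Days strictly between the two visits that fall in June to October:

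| First dose | D84 to D168 | Days in season (84-day gap) | Share of 153 | Days in season (73-day gap) | Share of 153 |
|---|---|---|---|---|---|
| 1 March | 24 May to 16 August | 76 | 50% | 69 | 45% |
| 15 March | 7 June to 30 August | 83 | 54% | 72 | 47% |
| 31 March | 23 June to 15 September | 83 | 54% | 72 | 47% |
| 14 April | 7 July to 29 September | 83 | 54% | 72 | 47% |

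Flow-chart days are counted here from each child's own first dose. For group 2 the gap is the same length and runs from about study day 98 to 182.

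**The case against.** The strongest reply is that this is a mismatch between two passages, not a proven hole in the plan. The protocol gives neither passage precedence, and if section 3 governs there is no gap. The schedule text is also loose elsewhere: section 5.2.3 counts 11 clinic visits, while the flow chart and section 5.2.4 list ten. This stands as far as it goes, and the finding is framed accordingly. Still, the flow chart, footnote, visit total and clinic-day list all agree with each other against section 3. An unidentified eleventh clinic visit would not supply two monthly home visits.

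Section 15.1.3 lists samples on D112 and D140. It uses visit numbers up to V50 that the flow chart does not have, and its days conflict with section 15.1.1 and the synopsis. It cannot be counted as scheduled contact.

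Several stronger readings are tempting, and the documents do not support them:

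- **No contact at all.** Families are told to report if the child is unwell, medical care is paid for, and the costs of unscheduled visits are reimbursed. What is missing is scheduled, active contact.
- **A breach of 24-hour notification.** Under section 13.4.3 the clock starts when the investigator is alerted. An SAE found late is reported late without breaking the rule.
- **Active visits only in the low season.** On the assumed dates D168 falls between 16 August and 29 September, and D196 between 13 September and 27 October. Every child has both inside the season. Section 1.2 also names no peak within June to October, so it cannot be said that the gap opens at the worst moment.
- **A compromised go/no-go decision.** That analysis is at D84, before the gap opens. Scheduled dosing and the solicited and 28-day unsolicited periods are over by then.

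It is also fair that deaths and admissions can still be elicited at D168. That limits the loss of events, but not the delay or the weaker dating.

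**Conclusion.** The contradiction is real and should be resolved. Section 3 promises monthly active SAE collection from D84, and the schedule delivers it only from D196. If the schedule is followed, the longest planned interval without contact in that period is three times the 28 days that section 3 implies (84/28 = 3), and it covers roughly half of the high-transmission season.

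The 84 days and the two missing visits follow directly from the protocol. The seasonal share rests on the planned March 2007 start and the assumed range of first doses; the lower figure of 45-47% rests on reading the windows as plus or minus. The effect is confined to late SAEs and the end-of-study annex safety analysis.

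**What to change.** Bring the schedule into line with section 3. Add monthly home visits to record SAEs at about D112 and D140 to the synopsis flow chart, renumber the monthly series HV16 to HV23, and correct the footnote and the total in section 5.2.3 to 23 home visits. Use the same SAE recording as at the visits from D196.

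The cost is a schedule amendment and 2 x 45 = 90 field-worker visits, fewer if children drop out, by a team already making such visits. Section 3 already commits to this work. Rewording section 3 to match the flow chart would also remove the contradiction, but it would leave the 84-day interval in place.
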